### Secondary outcomes

Change in functional exercise capacity will be assessed using the 6MWD, obtained from 6MWT. The 6MWD is responsive to change following exercise training in ILD [49]. Two tests will be conducted at each time point, according to international standards [49], to control for the known learning effect with the best distance recorded [49]. Supplemental oxygen will be used during the 6MWTs in those participants already receiving oxygen therapy with flow rates held constant for subsequent tests.

Health related quality of life (HRQoL) will be measured using the St George’s Respiratory Questionnaire IPF specific version (SGRQ-I), and the Chronic Respiratory Disease Questionnaire (CRQ). Both the CRQ and SGRQ-I have been validated in ILD and are responsive to change following exercise training [9, 50].

The Dyspnoea-12 and Modified Medical Research Council (mMRC) dyspnoea scale will be used to assess change in dyspnoea. The Dyspnea-12 assesses breathlessness severity incorporating both the physical and emotional components and has demonstrated reliability in ILD [51–53]. The mMRC is a single five-point scale used to measure the degree of disability that breathlessness poses on day-to-day activities and is a valid measure of dyspnoea and symptom severity in ILD [54–56]. Change in fatigue will be measured using the Fatigue Severity Scale (FSS). The FSS is a valid, sensitive measure in ILD with responsiveness to change following exercise training [57, 58]. Anxiety and Depression will be evaluated using the Hospital Anxiety and Depression Scale (HADS), a validated and widely used tool for assessing psychological distress [59, 60].

Cross-sectional area of the quadriceps will be measured by B-mode ultrasonography to assess changes in muscle size. Ultrasonography is a valid and reliable non-invasive method to measure quadriceps muscle size [61] and it has previously used to measure quadriceps cross-sectional area in COPD and ILD patients [17, 62, 63].

Sedentary behaviour and time spent in physical activity of various intensities (light, moderate, vigorous) will be measured by the GENEActiv actiwatch (ActivInsights Ltd, Kimbolton, Cambridgeshire, United Kingdom), a wrist-worn, waterproof, tri-axial accelerometer with demonstrated validity in measuring physical activity energy expenditure in IPF [64]. Participants will wear the GENEActiv actiwatch continually for 7 days in order to accurately capture all activity intensities [65].

A global rating of change scale will be used to assess the participants’ self-perceived improvement or deterioration in their symptoms and walking ability upon completion of the intervention [66]. The proportion of participants who a) complete the program and b) adhere to the planned exercise protocol will be compared between MICT and HIIT at eight weeks. Attendance of at least 75% of planned sessions will be defined as completion of the intervention [67]. Serious adverse events will be monitored and recorded prospectively during the duration of the study. Adverse events will be defined as progression of fILD (acute respiratory deterioration, development of resting hypoxaemia); acute exacerbation of fILD, musculoskeletal injury, lower limb pain, fainting, dizziness, chest pain, hospitalization; or death. Participants who experience an adverse event will receive all necessary medical care from their local health care team.

### Sample size

A total of 122 participants (61 per group) will be required to detect a clinically important difference between groups for the primary outcome measure of exercise endurance in the CWRT, with 80% power, and at the two-sided 5% level. This is based on the intermediate boundary (150 s) of the mean important difference range for the CWRT (SD = 292 s) [46, 68]. We will also be powered for the secondary outcome of HRQoL measured by the SGRQ-I based on data from our previous RCT of exercise training in ILD [11]. For HRQoL, a total of 114 participants are required to detect a mean difference of 6 points in SGRQ-I total score (SD = 11.3 points). In our previous trial, we had 5% attrition at completion of exercise training and 12% attrition at six months follow up [11]. Therefore, we will randomise a total of 130 participants, split evenly between groups.

### Statistical analysis

Continuous outcome variables will be analysed using linear mixed models, controlling for recruitment site and baseline values as required. All data will be analysed by intention to treat, with inclusion of all available data regardless of whether the intervention is completed. The proportion of participants who completed the program, adhered to the exercise training protocol and had an adverse event will be compared between groups using a chi-squared test. Alpha will be set at 0.05.

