### Recruitment and randomisation

Potential participants will be identified by (1) their treating physician or ILD nurses when attending the respiratory medicine clinic or (2) when they are referred to PR program at the participating sites. Eligible participants will be provided with written and verbal information about the study from a clinician and/or a researcher. Patients will be informed that participation in the study is voluntary and their decision regarding participation will have no effect on their treatment, their relationship with their healthcare team or any other healthcare requirements. All participants will provide written informed consent.

Following the completion of the baseline assessments, patients will be randomly allocated to receive MICT or HIIT using a computer generated, permuted block randomisation scheme stratified for (i) SpO_2_ < or ≥ 90% during 6-min walk test (6MWT) on room air, to ensure that those who desaturate are evenly distributed between the intervention and control group, and (ii) site of recruitment. Sequence generation will be performed by an individual independent of the research team and the group allocation will be concealed using a secure online database. An independent assessor, blinded to group allocation, will perform the outcome assessments at each timepoint. Given the physical nature of the intervention (exercise training) participants will not be blinded to group allocation. The flow of participants through the study will be reported according to the recommendations from the Consolidated Standards of Reporting Trials statement [38] and is outlined in Fig. 1.

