### Primary outcome

The primary outcome is change in endurance time measured using the CWRT on a cycle ergometer at 80% of Wpeak achieved on a baseline CPET according to the standardised criteria [37, 45, 46]. All tests will be performed on room air. The CWRT will be terminated before volitional symptom limitation if SpO_2_ < 78%. Endurance time is considered the most responsive outcome for evaluating exercise-related physiological changes following therapeutic interventions in COPD [45–47] and IPF [48].

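### The stated model for continuous outcomes leaves out the SpO2 stratum used in randomisation; if that stratum is prognostic, the analysis is slightly conservative and gives up a little power

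*Protocol article*

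**What the plan says.** The protocol article, under Recruitment and randomisation, describes a "permuted block randomisation scheme stratified for (i) SpO_2_ < or ≥ 90% during 6-min walk test (6MWT) on room air", with recruitment site as the second factor. It gives the purpose of the SpO2 factor: "to ensure that those who desaturate are evenly distributed between the intervention and control group".

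Under Statistical analysis, the model is given in one sentence: "Continuous outcome variables will be analysed using linear mixed models, controlling for recruitment site and baseline values as required". Site is named and the SpO2 stratum is not. No other section adds it.

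Two further statements bear on the point. Under Primary outcome, the constant work rate test is done on room air and has a saturation limit: "The CWRT will be terminated before volitional symptom limitation if SpO_2_ < 78" (per cent). Under Sample size, the calculation is made "with 80% power, and at the two-sided 5% level" and rests on "the intermediate boundary (150 s) of the mean important difference range for the CWRT (SD = 292 s").

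**The concern.** The design treats desaturation as important enough to balance by stratification, but the stated analysis does not use it. When a factor is balanced by design, the treatment estimate no longer varies through chance imbalance on it. A model without the factor still counts its variance as residual noise. If the factor predicts the outcome, the model-based standard error is then larger than the real sampling error, intervals are too wide, and the test rejects less often than its nominal level.

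The document makes a link to the primary outcome plausible, because low saturation can end the endurance test before symptoms do. At stake is some precision that the stratified design has already made available.

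The wording adds a second, smaller problem. Baseline values most naturally means the baseline score of each outcome, and the qualifier at the end of the sentence leaves it open which covariates enter which model.

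**Working it through.** **Inputs from the Sample size section:** difference 150 s, SD 292 s, two-sided alpha 0.05, power 80%, 61 per group. **Not in the document:** the share of outcome variance that the SpO2 stratum explains after site and baseline. Call it R² and take 0 to 0.10 as an assumed range. The SD of 292 s is taken as the residual SD after site and baseline.

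**Step 1, the plan's own figure.** The normal approximation gives n per arm = 2 × (1.960 + 0.842)² × (292/150)² = 59.5, so 60 per arm (120). The two-sample t-test version gives 60.46, so 61 per arm, which is the stated 122. Power at 61 per arm is 81.0% (normal) or 80.4% (t). The stated figure is reproduced, and the calculation uses a single SD with no stated reduction for covariates.

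**Step 2, stratum omitted or included.**
- Reported SE without the stratum: 292 × √(2/61) = 52.9 s.
- True SE under stratified allocation: 52.9 × √(1 − R²).
- Power, omitted: Φ((150 − 1.96 × SE reported) / SE true).
- Power, included: Φ(150 / SE true − 1.96).
- Actual type I error, omitted: 2 × (1 − Φ(1.96 × SE reported / SE true)).

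Example at R² = 0.05: true SE = 52.87 × √0.95 = 51.5 s. Power omitted = Φ(46.4/51.5) = Φ(0.900) = 81.6%. Power included = Φ(150/51.5 − 1.96) = Φ(0.951) = 82.9%.

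| R² beyond site and baseline | True SE (s) | Reported SE too large by | Type I error, omitted | Power, omitted | Power, included | Forgone (points) |
|---|---|---|---|---|---|---|
| 0 | 52.9 | 0% | 5.0% | 81.0% | 81.0% | 0 |
| 0.02 | 52.3 | 1.0% | 4.8% | 81.2% | 81.7% | 0.5 |
| 0.05 | 51.5 | 2.6% | 4.4% | 81.6% | 82.9% | 1.3 |
| 0.10 | 50.2 | 5.4% | 3.9% | 82.2% | 84.9% | 2.7 |

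A simulation with 122 analysed, four equal sites, 60% desaturators and permuted blocks of four (the last three are assumptions), 3,000 trials per setting and site in both models agrees. Power was 81.3% against 83.0% at R² = 0.05, and 82.1% against 84.6% at 0.10.

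**Step 3, what baseline adjustment does to R².** Suppose the stratum alone explains a share r² of the variance of both the baseline and the follow-up value, and the two values correlate at ρ. The share left after baseline is r²/(1 − r²) × (1 − ρ)/(1 + ρ). With ρ from 0.5 to 0.7 (assumption):
- r² = 0.10: 0.111 × 0.333 = 0.037 at ρ = 0.5, and 0.111 × 0.176 = 0.020 at ρ = 0.7. The SE is 1.0% to 1.9% too large and the forgone power is 0.5 to 1.0 points.
- r² = 0.20: 0.25 × 0.333 = 0.083, and 0.25 × 0.176 = 0.044. The forgone power is 1.2 to 2.2 points.

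**The case against.** The strongest case against acting has three parts.

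**An unseen analysis plan may add the stratum.** A one-sentence model in a journal article is a summary, its closing qualifier leaves room, and the SpO2 category comes from a test done before randomisation. Part of this stands: the wording does not forbid the stratum, and a fuller document may include it. But the sentence is not silent on covariates. It names one of the two randomisation factors and not the other, so the published statement should be made to match the design in any case.

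**The stratum may not be prognostic.** The document gives no figure. The primary outcome is a change in endurance time, on a test set at 80% of each participant's own peak work rate, which partly evens out capacity. The stopping limit of 78% on the cycle test and the 90% cut on the walk test do not define the same group. This stands, and it is why the loss is conditional and can be zero.

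**Baseline adjustment absorbs much of any stable effect.** This also stands, as Step 3 shows. A reader might infer a loss of five power points from a stratum explaining 20% of outcome variance. That holds only if the 20% remains after baseline. Under the Step 3 relation, the stratum alone would then have to explain about 38% (ρ = 0.5) to 53% (ρ = 0.7) of the variance.

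Two other stronger readings are tempting. One is that the trial is underpowered or its p-values invalid. The documents do not support this: 122 gives the stated 80% power without the stratum, and the error is in the conservative direction. The other is that the chi-squared comparisons of proportions need the same change. The calculation covers continuous outcomes only and gives no basis for that.

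**Conclusion.** The mismatch between design and stated model is real, and its consequence is small and conditional. If the SpO2 stratum carries information beyond site and baseline, the reported standard error is about 1% to 5% too large and 0.5 to 2.7 power points are forgone for R² between 0.02 and 0.10. If it carries none, nothing is lost. The treatment estimate is not biased, and type I error stays at or below 5%.

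The size rests on the plan's 61 per arm, 150 s and 292 s, on near-balance within strata, and on an assumed R². If 292 s is instead the SD before baseline adjustment, power is already about 91% to 98% for ρ between 0.5 and 0.7, and the gain shrinks to between 0.1 and 1.3 points for r² of 0.10 to 0.20. This is a low-cost improvement to the primary analysis and does not correct a failing one.

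**What to change.** Replace the model sentence under Statistical analysis with wording to this effect: all linear mixed models for continuous outcomes will include, as fixed effects, both randomisation factors (SpO2 stratum on the room-air 6-minute walk test, and site) and the baseline value of the outcome. Delete the closing qualifier, so that the covariates are fixed before the data are seen. If a separate analysis plan exists, make the same statement there.

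The cost is one sentence and one degree of freedom. The stratum is known for every participant at randomisation, so no new data are needed. The sample size and the comparisons of proportions stay as they are.

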### Interventions

Participants in both groups will undergo a standard 8-week twice-weekly supervised PR at the centre where they were recruited. Each session will consist of lower limb aerobic training plus upper and lower limb resistance training exercises. The intensity (high versus moderate) and the type (continuous versus interval) of aerobic exercise training will differ between the two intervention groups.

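### Completion, adherence and adverse events are to be compared with an unadjusted chi-squared test although randomisation is stratified by site; a site-stratified analysis would be a free, minor gain

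*Protocol article*

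**What the plan says.** The Statistical analysis section of the protocol article handles the two kinds of outcome differently. Continuous outcomes go into linear mixed models that control for recruitment site and baseline values as required. For the binary outcomes, the proportions of participants who completed, "adhered to the exercise training protocol and had an adverse event will be compared between groups using a chi-squared test". No site term or stratification is named for that test. The section then adds: "Alpha will be set at 0.05".

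Recruitment and randomisation describes permuted blocks stratified by SpO2 below, or at or above, 90% during the 6-minute walk test, and by "ii) site of recruitment". Design names four sites. Under Interventions, each participant receives "supervised PR at the centre where they were recruited". Under Sample size, "we will randomise a total of 130 participants, split evenly between groups", and only the endurance time and SGRQ-I comparisons are sized.

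**The concern.** The trial randomises within sites but, for these three outcomes, is to be analysed as if it had not. Because participants train where they were recruited, attendance and adherence could plausibly vary by site. Blocking within site balances that variation between the arms, so it does not contribute to the difference between them. A crude test nevertheless includes it in the variance it divides by. The standard error is then too large, the test rejects less often than its nominal level, and power falls.

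What is at stake is modest: a somewhat greater chance of missing a real difference in completion or adherence. Adherence is part of the rationale in the Background, which suggests that fibrotic disease may limit adherence to continuous training and cites greater adherence with interval training in COPD. Nothing here touches the primary outcome.

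**Working it through.** **The plan's own figures.** The inputs are "intermediate boundary (150 s) of the mean important difference range for the CWRT (SD = 292 s"), "with 80% power, and at the two-sided 5% level".
- Normal approximation: n per arm = 2 × (1.960 + 0.842)² × (292/150)² = 2 × 7.85 × 3.79 = 59.5, so 60.
- The t-test version gives 60.46, so 61 per arm and 122 in total, as stated.
- For SGRQ-I (6 points, SD 11.3) the t-test version gives 56.66, so 57 per arm and 114 in total, as stated.

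Both totals reproduce. No rate, power or sample size is given for completion, adherence or adverse events, so everything below rests on assumed rates.

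**Why the crude test is conservative when sites differ.** Let site k hold share w of the participants and have rate p under no treatment effect. The crude test uses the variance p̄(1 − p̄), where p̄ = Σwp. With balance within site, the difference between arms actually varies according to Σwp(1 − p). With R = Σwp(1 − p) / [p̄(1 − p̄)], the approximate true level is 2 × [1 − Φ(1.96/√R)].

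Assumed site shares: 35/25/20/20%.

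| Site rates | p̄ | p̄(1 − p̄) | Σwp(1 − p) | R | 1.96/√R | True level |
|---|---|---|---|---|---|---|
| Equal, e.g. 80% | 0.80 | 0.160 | 0.160 | 1.00 | 1.96 | 5.0% |
| 60/70/85/95% | 0.745 | 0.190 | 0.1715 | 0.903 | 2.06 | 3.9% |
| 40/60/80/95% | 0.64 | 0.230 | 0.1855 | 0.805 | 2.18 | 2.9% |

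**Simulation of level and power.** Assumptions: 130 participants, the same site shares, 70% desaturators with completion 10 points lower, blocks of 4 within the 8 site-by-desaturation strata, the listed rates in the HIIT arm and, for power, MICT 20 points lower; 20,000 trials per setting.

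| Site rates | Level, crude | Level, stratified | Power, crude | Power, stratified |
|---|---|---|---|---|
| No site differences | – | – | 63.8% | 63.9% |
| 60/70/85/95% | 4.1% | 5.0% | 64.7% | 68.1% |
| 40/60/80/95% | 2.9% | 4.9% | 63.5% | 72.6% |

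The power losses are 68.1 − 64.7 = 3.4 points and 72.6 − 63.5 = 9.1 points. A repeat run gave crude levels of 3.7% and 3.0% in the two unequal settings.

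**Milder and more extreme settings.** A separate simulation used site shares 40/25/20/15%, an odds ratio of 2.5 for power and 6,000 trials per setting.

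| Site rates | Level, crude vs stratified | Power, crude vs stratified |
|---|---|---|
| Equal, 20% | 0.050 vs 0.050 | 0.65 vs 0.65 |
| 15-30% | 0.050 vs 0.053 | 0.64 vs 0.65 |
| 10-40% | 0.047 vs 0.052 | 0.58 vs 0.61 |
| 60-95% | 0.041 vs 0.050 | 0.47 vs 0.50 |
| 5-60% | 0.029 vs 0.051 | 0.44 vs 0.55 |

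The loss is negligible for mild differences and grows with the spread between sites.

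**Rare events.** With 65 per arm, fewer than 5 events are expected per arm if the rate is below 5/65 = 7.7%. For 0 versus 4 events the uncorrected chi-squared test gives p = 0.042 and Fisher's exact test p = 0.119. Here the large-sample approximation is the weak point, and the direction is the opposite of conservative.

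**The case against.** The strongest reply is that the chi-squared test is valid, that its loss depends entirely on differences between sites, and that the documents report none. The Interventions section says that training and weekly progression are standardised across sites. Under Secondary outcomes, one attendance threshold for completion and one list of adverse events apply everywhere. All of this may narrow site differences. The outcomes are not primary, and the contrast with the continuous models is softened because those control for site only as required. Each of these points stands. They limit the size of the point, but they do not give a reason to prefer the unadjusted test, which has no appreciable power advantage in the settings above.

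Two stronger readings are tempting, and the documents support neither.

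- A reader might infer that these tests are conservative as a matter of fact. That would need site rates, which are not given. With equal or mildly different rates the level stays at 5%, and with rare events the uncorrected test can be more liberal than an exact one.
- A reader might infer that a non-significant adverse-event result could not be interpreted because site is ignored and no effect size is named. The limit there is the trial's size. At an assumed 20% event rate in both arms, the 95% interval half-width is 1.96 × √(2 × 0.2 × 0.8/65) = 0.138, about 14 points, and power for 10% versus 20% is about 36%. Stratifying by site would not materially change that. A condensed article may also leave effect measures and intervals to the full protocol or analysis plan, and nowhere does it say that p > 0.05 will be read as equal safety.

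**Conclusion.** The point holds as a minor one. The article fixes an unadjusted test for three outcomes in a trial randomised within sites. That test is valid but can waste power. The cost runs from nothing when sites are alike, through about 3 points of power with completion of 60-95% across sites, to about 9 points at 40-95%; the true type I error is then about 5%, 4% and 3% respectively. These figures rest on assumed site rates and shares, blocks of 4 and a 20-point effect. No invalid inference and no contradiction is shown. The primary analysis and the stated sample sizes are unaffected.

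**What to change.** In Statistical analysis, replace the chi-squared test for the three proportions by a Cochran-Mantel-Haenszel test stratified by recruitment site, adding the desaturation stratum where cell counts allow. Logistic regression with site is an acceptable alternative. Report the stratified risk difference (after logistic regression, the marginal one) with its 95% confidence interval, so that the range of differences still compatible with the data is visible. State in advance that sparse strata will be pooled, or an exact stratified test used, where events are rare.

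The cost is a sentence or two of wording and a little programming, with no change to recruitment, data collection or sample size. The one drawback is that with very few events some site strata carry no information, which the pooling or exact-test rule covers.

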### Data integrity, management and monitoring

Hardcopy original data collection forms will be kept in a locked filing cabinet within a locked office. Electronic data will be stored in a purpose-built on-line database (www.adeptrs.com), with encryption and password protection. No identifying information will be stored in the online database. Electronic data for all sites will be accessible by the principal investigator and the trial coordinator. Site specific investigators will only have access to data relating to their individual site. The trial will be monitored by an independent Data Safety and Monitoring Committee (DSMB), chaired by a respiratory physician who is independent of the study team and trial sites. Any serious adverse events will be notified to the overseeing ethics committee (Alfred Health) and the relevant site governance committee, as well as to the DSMB.

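### The one stated safety test pools disease events and deaths with training-type events, which dilutes any excess specific to high intensity interval training (HIIT)

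*Protocol article*

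**What the plan says.** Statistical analysis in the protocol article plans that the proportion who "had an adverse event will be compared between groups using a chi-squared test", and adds: "Alpha will be set at 0.05". It names no comparison by type or seriousness of event, and no time window for this one.

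The definition is under Secondary outcomes. It opens with "Adverse events will be defined as progression of fILD (acute respiratory deterioration, development of resting hypoxaemia" and continues with "acute exacerbation of fILD, musculoskeletal injury, lower limb pain, fainting, dizziness, chest pain, hospitalization; or death". All of these count equally towards one yes/no variable.

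The sentence just before the definition reads: "Serious adverse events will be monitored and recorded prospectively during the duration of the study". Under Data integrity, management and monitoring, serious events are also reported to the ethics committee, the site governance committee and the independent safety board.

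The Sample size section powers the trial for endurance time and for the SGRQ-I quality-of-life score. It gives no event rate or detectable difference for safety.

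**The concern.** The arms differ only in the intensity and type of aerobic training, and training lasts 8 weeks. Follow-up runs six months beyond that, in a population that the Background describes as partly progressive with poor prognosis. The events most plausibly affected by the contrast are the musculoskeletal, leg-pain, dizziness, fainting and chest-pain items. Progression and exacerbation of the lung disease can be expected in both arms whatever the training.

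With a single yes/no variable, a participant whose disease progresses is already counted, so a training injury in that person adds nothing to the comparison. The difference between arms shrinks while its variance usually grows. The article presents this as the first randomised comparison of the two methods over an 8-week programme in fibrotic disease. A non-significant pooled result could therefore be taken as reassurance that the test is poorly placed to give.

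**Working it through.** **Inputs from the article.** 130 randomised and split evenly, so 65 per arm (Sample size). Two-sided 5% level (Sample size; Statistical analysis repeats 0.05). The plan has no safety figure to reproduce. Its stated sample sizes do reproduce: a t-test calculation for 150 s with SD 292 s at 80% power gives 60.46, so 61 per arm and 122 in total. For 6 points with SD 11.3 it gives 56.66, so 57 per arm and 114 in total.

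**Assumed inputs.** All event rates are assumptions, because the article gives none. Let c and t be the risks of a training-type event under moderate continuous training and HIIT. Let b be the background risk of a disease event, equal in both arms and independent of training-type events.

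**Formulas.**
- Pooled risk in each arm: p1 = 1 − (1 − b)(1 − c) and p2 = 1 − (1 − b)(1 − t).
- The pooled difference is therefore (1 − b)(t − c), smaller than t − c whenever b is above zero.
- Power = Φ[(|p2 − p1| − 1.96·SE0)/SE1], with SE0 = √[2·p̄(1 − p̄)/n], SE1 = √[p1(1 − p1)/n + p2(1 − p2)/n], p̄ the mean of p1 and p2, and n = 65.

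**Worked case, 20% versus 5%.**
- Separate test: p̄ = 0.125, SE0 = 0.0580, SE1 = 0.0565. Power = Φ[(0.15 − 1.96 × 0.0580)/0.0565] = Φ(0.64) = 74%.
- Pooled with b = 0.40: p1 = 1 − 0.60 × 0.95 = 0.43 and p2 = 1 − 0.60 × 0.80 = 0.52. The difference falls from 0.15 to 0.09, with SE0 = 0.0876 and SE1 = 0.0872. Power = Φ(−0.94) = 17%.

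**Range.**

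| HIIT vs continuous | Separate | Pooled, b = 10% | 20% | 30% | 40% | 50% |
|---|---|---|---|---|---|---|
| 15% vs 5% | 48% | 26% | 17% | 13% | 10% | 8% |
| 20% vs 5% | 74% | 47% | 32% | 23% | 17% | 14% |
| 25% vs 10% | 62% | 42% | 30% | 23% | 17% | 14% |
| 30% vs 10% | 82% | 63% | 48% | 36% | 28% | 21% |

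Pooling costs power in every cell. The last row also shows that a large excess over a low background keeps 63%. Even unpooled, 80% power needs about 22% against 5%, or 29% against 10%.

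**Sensitivity to recording.** If only half of the training-type events were captured in both arms, the separate test for 20% versus 5% would compare 10% with 2.5%, and its power would fall from 74% to 42%. This shows why the recording question is worth settling. It is not evidence that capture is incomplete.

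**The case against.** The strongest reply is that this is a condensed article. Tables by event type, effect estimates and rules for small counts commonly belong to the full protocol or the analysis plan, and nothing in the article rules them out. That stands as far as reporting goes. It does not remove the point, because the article does choose a between-group test, and the one it names is the pooled one.

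Three stronger readings are tempting, and the article does not support them.

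- *Harm from HIIT will probably be missed because of pooling.* This depends on rates that are not given. People with anticipated death or transplantation are excluded, and the Design section expects no excessive loss from either, so a high background cannot be taken as fact. Much of the low power also comes from 65 per arm: three of the four separate tests above stay below 80%.
- *Only serious events are recorded prospectively.* The sentence on serious events does not say that others are left out. The article defines non-serious events and plans to compare them, which implies collection. The twice-weekly supervised sessions and weekly diary review offer occasions for it. This is an ambiguity.
- *The trial will claim equal safety from a p-value.* No section plans such a claim, and the stated hypothesis and intended conclusions concern exercise tolerance, symptoms and quality of life. Serious events also go to an independent board.

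A further objection concerns the remedy. Sorting events by presumed cause would rely on staff who know the allocation. Placing every admission and death under disease would hide any that arose from training. Both points stand, and they shape the fix.

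**Conclusion.** The point holds in limited form. The stated safety comparison combines unlike events, and any background of disease events common to both arms dilutes an excess confined to training-type events. For an assumed 20% versus 5% at 65 per arm, power falls from 74% to between 47% and 14% as the assumed background rises from 10% to 50%. The direction held in every scenario examined. The size rests on assumed rates, on equal background in the two arms and on independence of the two kinds of event. Separate comparisons would themselves be underpowered for smaller excesses (48% for 15% versus 5%), so interval estimates matter more than tests. How non-serious events are recorded needs clarifying and is not a demonstrated fault.

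**What to change.** Keep the all-event comparison, which needs no attribution. Add three comparisons, defined by the event types already listed under Secondary outcomes and without any judgement of cause:

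1. Training-type events with onset in the 8-week training period: chest pain, dizziness, fainting, leg pain or musculoskeletal injury.
2. Progression or acute exacerbation of the lung disease, over the whole study.
3. Hospitalisation or death, over the whole study, as its own category.

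Report each as a risk difference with a 95% confidence interval, and use an exact test where expected counts are small. State that a non-significant result will not be read as equal safety. Add one sentence saying how and when the non-serious listed events are collected, and that the method is the same in both arms.

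The cost is a few more unpowered comparisons and a little more analysis. Sample size, treatment and visits do not change. The first category needs event type and onset date on record. Recruitment began in July 2019, so if those details were not kept for early participants, a later change in wording cannot recover them, and the report should say so.
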